# A multicentre parallel-group randomised trial assessing multiparametric MRI characterisation and image-guided biopsy of prostate in men suspected of having prostate cancer: MULTIPROS study protocol

**DOI:** 10.1186/s13063-019-3746-0

**Published:** 2019-11-21

**Keywords:** Prostate cancer, Multiparametric magnetic resonance imaging, Prostate biopsy

## Abstract

**Background:**

There is growing evidence suggesting that multiparametric magnetic resonance imaging (mpMRI) is a marker for prostate cancer (PCa) aggressiveness and could be used to plan treatment. Improving early detection of clinically significant PCa with pre-biopsy mpMRI would very likely have advantages including optimising the diagnosis and treatment of diseases and diminishing patient anxiety.

**Methods and materials:**

This is a prospective multicentre study of pre-biopsy mpMRI diagnostic test accuracy with subgroup randomisation at a 1:1 ratio with respect to transrectal ultrasound (TRUS) and MRI/US fusion-guided biopsy or TRUS-only biopsy. It is designed as a single-gate study with a single set of inclusion criteria. The total duration of the recruitment phase was 48 months; however, this has now been extended to 66 months. A sample size of 600 participants is required.

**Discussion:**

The primary objective is to determine whether mpMRI can improve PCa detection and characterisation. The key secondary objective is to determine whether MRI/US fusion-guided biopsy can reduce the number of false-negative biopsies. Ethical approval was obtained from the East of Scotland Research Ethics Committee 1 (14/ES/1070) on 20 November 2014. The results of this study will be used for publication and presentation in national and international journals and at scientific conferences.

**Trial registration:**

ClinicalTrials.gov, NCT02745496. Retrospectively registered on 20 April 2016.

## Background

### Introduction and rationale

Men suspected of having prostate cancer (PCa) because of high levels of serum prostate-specific antigen (PSA) and/or abnormal digital rectal examination (DRE) are offered prostate biopsies guided by transrectal ultrasound (TRUS). Several challenges are seen in this crucial step. Firstly, the incidence of false-negative biopsies (i.e. clinically significant tumours not being detected) may be as high as 35% in first-time biopsies [1]; secondly, up to 44% of men younger than 70 years of age may need a second set of biopsies following initial negative results [2]; thirdly, up to 50% of PCa cases currently detected by these methods may not be clinically relevant when considering other patient-related factors; fourthly, data from UK Prostate Testing for Cancer and Treatment (ProtecT) has shown significant morbidity of the biopsy procedure, at times even leading to patient death [3]; and, finally, several studies have shown no improvement in PCa mortality, despite increased detection rates through screening programmes [4], and the number of deaths from PCa in the UK sadly remains largely unchanged.

Post-biopsy standard of care magnetic resonance imaging (MRI) is offered to patients with positive biopsy results or when there is a continuous increase in PSA levels despite negative biopsies. The performance of post-biopsy MRI in the staging and detection of PCa is significantly degraded by post-biopsy artefact [5, 6]. Therefore, it is recommended that MRI should be performed at least 10 weeks after biopsy, and if possible after 20 weeks [7]. Such a wait is unacceptable to patients and causes breaching of time with respect to treatment guidelines. Improving early detection of clinically significant PCa would very likely save many lives by refining the stratification of patients for optimising the treatment of significant disease, whilst simultaneously diminishing patient anxiety and morbidity through overdiagnosis and overtreatment.

### Objectives

The primary objective is to determine whether using multiparametric MRI (mpMRI) can improve cancer detection and the characterisation of PCa, and primary outcome measurements include:
Number of PCa cases detected by mpMRI when compared to gold-standard prostatectomy specimensNumber of clinically significant cancers detected by mpMRI when compared to gold-standard prostatectomy specimens

The secondary objective is to assess whether MRI/US fusion-guided biopsy can reduce the number of false-negative biopsies, and key outcome measurements include:
Number of cancers detected in each randomised group, namely the intervention group (TRUS and MRI/US fusion-guided biopsy) vs. the standard of care group (TRUS only biopsy)Number of clinically significant cancers detected in each randomised group

### Trial design

This is a prospective multicentre study of pre-biopsy mpMRI diagnostic test accuracy with subgroup randomisation at a 1:1 ratio with respect to TRUS and MRI/US fusion-guided biopsy or TRUS-only biopsy. This is the first large trial to randomise men into either targeted or non-targeted biopsy with pre-biopsy MRI and to choose radical prostatectomy histopathology using 3D fabricated moulds as the gold standard (Fig. 1).

**Fig. 1 Fig1:**
[figure not shown]
Design of the trial

## Methods/design

### Study population and setting

Prospective recruitment of men referred with suspected clinically localised PCa will be carried out in urology clinics. The number of patients screened for eligibility over the recruitment period is estimated to be 1000. The number of patients not eligible for the study is estimated to be 350 and the number of patients who are likely to decline is estimated to be 50. The number of participants who are likely to progress to pre-biopsy MRI is estimated to be 600. Local audit information suggests that after a positive diagnosis of PCa, around 25% of men will opt for radical surgery. Based on the recruitment of 600 eligible men, the lowest amount of complete data for radical prostatectomy histology for analysis will be *n* = ~ 150. Our power calculation based on 80% sensitivity and a precision of ± 9% and an AUROC = 0.9 suggests that we need a minimum of 80 men with complete datasets from imaging and histopathology of radical prostatectomy to answer the primary objective. The dropout rate and incomplete datasets have been taken into consideration in designing this study.

Rais-Bahrami et al. [8] suggest that 80% of all pre-biopsy MRI scans (*n* = ~ 600) will have lesions suspicious for PCa, regardless of the level of suspicion assigned by mpMRI (*n* = ~ 480). Based on such information, we calculated that each of the two randomisation arms will have approximately 240 patients.

Initially, the total duration of the recruitment phase was 48 months; however, this will now be extended to 66 months with approval from the funding body. It is estimated that approximately 600 participants will be recruited and will receive a pre-biopsy MRI scan.

Participants will then be divided into two groups based on the mpMRI results. The group with positive mpMRI (*n* = ~ 480) will be randomised to the intervention (TRUS and MRI/US fusion-guided biopsy) group (*n* = ~ 240) or the standard care (TRUS-guided biopsy) group (*n* = ~ 240). The group with negative mpMRI (*n* = ~ 120) will undergo standard care (TRUS-guided biopsy) with histological comparative analysis. Participants will be followed through to a definite treatment stage. At sites where local facilities allow and for those who will undergo radical prostatectomy, histological findings will be compared to the pre-biopsy MRI results (*n* = ~ 80). The active trial participation for each participant will be varied depending on sites’ local pathways.

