### Allocations and interventions

All enrolled participants will be offered 1.5 Tesla or 3.0 Tesla mpMRI prior to prostate biopsy where this is not already within the standard care pathway. A subgroup of participants with positive pre-biopsy MRI will be randomised into two further subgroups at a 1:1 ratio. Randomisation will be via TRUST, a web-based, good clinical practice (GCP)-compliant randomisation system run by the Health Informatics Centre (HIC). Randomisation will be implemented with random block sizes stratified by site and minimised by: the Prostate Imaging Reporting and Data System (PI-RADS) suspicion score (3–5); index lesion size (in two categories: above and below 6 mm in maximal diameter on MRI); age (40–59 years, 60–75 years); and PSA < 10.1 or PSA ≥ 10.1 to ≤ 20 ng/ml). The first subgroup will undergo a TRUS and MRI/US fusion-guided biopsy and the second will undergo standard of care TRUS-guide biopsies only. The MRI/US fusion-guided biopsy will be performed during the same attendance as the TRUS-guided biopsy***.*** TRUS and MRI/US fusion-guided biopsies will be performed by NHS-accredited radiologists and/or urologists from the research team. The persons undertaking the biopsy will have prior experience and will have received appropriate training from clinical experts and/or the equipment supplier’s application specialist(s). Those participants with negative pre-biopsy MRI will follow the local standard of care pathway; where this includes biopsy, data from the biopsy will be collected for analysis.

In a subgroup of patients who undergo radical prostatectomy, the prostatectomy specimen will be sectioned using customised moulds [9, 10] allowing for direct comparison with mpMRI. This will be carried out in NHS Tayside, NHS Grampian and other sites where local facilities allow. Comparison of mpMRI with a reference standard of radical prostatectomy pathology will be performed as the primary outcome.

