## Trial status

The favourable approval for this trial was obtained from the East of Scotland REC 1 (Ref: 14/ES/1070) on 20 November 2014. The first patient was enrolled on 17 February 2015, with 416 participants so far recruited. The total duration of the recruitment phase was 48 months; however, this has now been extended to 66 months. The recruitment is scheduled to finish on 30 June 2020.

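### The forecast of about 150 prostatectomy datasets applies a surgery rate for diagnosed men to all 600 men with suspected cancer, so it is the highest expected yield, not the lowest

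*Protocol article*

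**What the plan says.** All the planning figures are in the protocol article, Study population and setting.

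- The men recruited have suspected disease: "Prospective recruitment of men referred with suspected clinically localised PCa will be carried out in urology clinics".
- The number reaching MRI: "The number of participants who are likely to progress to pre-biopsy MRI is estimated to be 600".
- The surgery rate and its base: "Local audit information suggests that after a positive diagnosis of PCa, around 25% of men will opt for radical surgery".
- The forecast drawn from these: "Based on the recruitment of 600 eligible men, the lowest amount of complete data for radical prostatectomy histology for analysis will be" about 150.
- The requirement: at least 80 men with complete imaging and prostatectomy histology, from a sensitivity of 80%, a precision of ±9% and an AUROC of 0.9.
- On losses: "The dropout rate and incomplete datasets have been taken into consideration in designing this study". No figure is attached.
- At the end of the section, the comparison of prostatectomy histology with MRI is put at about 80 men, at sites that have the facilities.

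Allocations and interventions makes this comparison the primary outcome. Of the mould-based sectioning on which it depends it says: "This will be carried out in NHS Tayside, NHS Grampian and other sites where local facilities allow".

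**The concern.** The surgery rate and the forecast stand in adjacent sentences but use different denominators. The rate applies once a man has been diagnosed; the forecast multiplies it by every man recruited on suspicion. That is correct only if all 600 turn out to have cancer. The article itself does not expect this: it models cancer as a yes/no outcome, and it anticipates about 120 MRI-negative men, who are biopsied only if their local pathway includes it.

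The direction of the error matters. Calling 150 the lowest amount of complete data tells the reader that the requirement of 80 is covered almost twice over. Undiagnosed men, sites without mould facilities and incomplete records can only reduce the number. The gap between 150 and 80 is the only numerical margin the article shows for its primary objective, so anyone judging whether that objective can be met relies on a figure biased upwards.

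**Working it through.** **Inputs from the article:** 600 recruits; 25% surgery rate among diagnosed men; minimum of 80 complete datasets; sensitivity 0.80; precision ±0.09; about 480 MRI-positive and 120 MRI-negative men.

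**Not in the article, so assumed:** the proportion diagnosed, p; the share of prostatectomies giving complete mould-sectioned data, c; a two-sided 95% confidence level; sensitivity counted per man.

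**1. Reproduce the forecast.** 600 × 0.25 = 150. The match is exact and implies p = 1 and c = 1. The 600 contains no post-entry deduction either: 1000 screened − 350 ineligible − 50 declining = 600.

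**2. Correct the denominator.** Expected prostatectomies = 600 × p × 0.25 = 150p. As p cannot exceed 1, 150 is the maximum expected value. For illustration, if all 480 MRI-positive men and no MRI-negative man had cancer, the yield would be 480 × 0.25 = 120.

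**3. Reproduce the requirement.** The simple formula gives n = 1.96² × 0.80 × 0.20 / 0.09² = 75.9, so 76 men. At n = 80 the half-width is 1.96 × √(0.16/80) = 8.8%. The stated 80 is thus slightly above the formula. The part played by the AUROC of 0.9 cannot be reconstructed.

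**4. Yield and precision over a range of p, with no losses.** Half-width = 1.96 × √(0.16/n). The probability of at least 80 is binomial with 600 trials and success probability 0.25p.

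| Assumed p | Expected prostatectomies | Half-width | P(at least 80) |
|---|---|---|---|
| 0.40 | 60 | ±10.1% | 0.005 |
| 0.50 | 75 | ±9.05% | 0.29 |
| 0.60 | 90 | ±8.3% | 0.89 |
| 0.70 | 105 | ±7.7% | 0.998 |
| 0.80 | 120 | ±7.2% | 1.00 |
| 1.00 | 150 | ±6.4% | 1.00 |

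**5. Break-even.** An expected 80 needs p = 80/150 = 53.3%, or 320 men diagnosed, with no losses. The 76 men needed for ±9% require p = 76/150 = 50.7%.

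**6. Break-even with losses (c assumed).** The required p is 80/(150c): 59.3% at c = 0.90 and 71.1% at c = 0.75. At c = 0.50 it is 106.7%, so an expected 80 is out of reach whatever the diagnosis rate.

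**The case against.** Five counter-arguments deserve an answer.

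*The margin may still be adequate.* A reader might infer from the denominator error that the margin over 80 has gone and the primary objective will fail. The article does not support that. At p = 0.60 the expected yield is 90, and at 0.70 it is 105. Some men are identified after a positive standard-care MRI, which could raise p. This objection stands: the size of the margin is unknown.

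*Missing 80 by a little costs little.* Also correct. Precision of ±9% needs 76 by the simple formula, 75 men give ±9.05%, and 60 give about ±10.1%. The loss is gradual.

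*The later figure of about 80 may be a different set.* It is tempting to call 150 and 80 a contradiction. The second figure is limited to sites with the facilities, so it can be read as a site-limited forecast within the 150. That reading is fair, but it does not repair the denominator, and a forecast equal to the minimum leaves no margin.

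*Losses were considered, and the detail may be in the full protocol.* An article may leave the derivation of a dropout allowance to the full document, so its absence is not the point. The gap from 150 to 80, (150 − 80)/150 = 46.7%, might itself be the intended allowance. But the article calls 150 the lowest amount of *complete* data, and that number contains no deduction. If the gap is the allowance, it must also absorb every undiagnosed man.

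*A yield of 150 could be exceeded.* It could, by chance or if the approximate 25% is too low. *Highest* here means the highest expected value under the article's own inputs.

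Nor should the interim recruitment count under Trial status be turned into a projected shortfall: recruitment was still open and the target remains 600.

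**Conclusion.** The point holds as an error in a stated planning figure for the primary outcome. Three parts need no assumption: the 25% was applied to the wrong denominator, 150 is the maximum expected yield and not a lower bound, and it deducts nothing for undiagnosed men, site facilities or incomplete data.

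How much this matters depends on a diagnosis rate the article does not give. Across assumed rates of 40% to 80% the expected yield is 40% to 80% of the stated figure, before losses. Whether 80 is reached depends on both p and completeness, so the defensible conclusion is a risk of shortfall. The likely harm at the lower end is an interval about one percentage point wider on each side than planned, and more if losses are added. The half-widths rest on the simple 95% formula with sensitivity counted per man.

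**What to change.** Under Study population and setting:

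1. Delete *lowest* and the claim that 150 is complete data.
2. Restate the yield as 600 × diagnosis rate × 0.25 × share of prostatectomies with complete mould-sectioned data, and give each factor a value.
3. Take those values from the men already in the study. Trial status reports: "The first patient was enrolled on 17 February 2015, with 416 participants so far recruited". Rates pooled over both randomised groups and the MRI-negative men are enough; no comparison between arms is needed. The audit-based 25% can be checked at the same time.
4. State the expected number that results and the precision it gives at 80% sensitivity, next to the required 80.
5. Say whether the later figure of about 80 is a site-limited forecast, the minimum repeated, or something else, and how it relates to about 150.

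The cost is a change of wording and a short pooled tabulation. The expected number will look less favourable, and the stated precision may too. No extra patients are needed.

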### Participant selection and enrolment

As standard care pathways differ among sites, the route of identification and screening of eligibility will differ in order to accommodate the local pathway. Potential participants will be identified by either the clinical team or the study team, with Caldicott Guardian Approval, depending on local practice.

#### Identifying potential participants

Potential participants may be identified through the following routes:
At the urology clinicFrom GP referrals to the urology teamBy the urology team after standard care mpMRI (positive results only)

#### Contacting potential participants

Contact will be made by either the clinical team or the study team through the following routes:
In person at clinicsThe clinical team will assess whether the patient meets the eligibility criteria for the study. If so, the study patient information sheet (PIS) will be given and a contact telephone number will be requested for a follow-up telephone call. A model PIS is shown in Additional file 1.Via letterThe clinical urological team will review GP referral letters or positive mpMRI results and identify patients who meet trial eligibility criteria. Those who met the eligibility criteria will be sent a clinic appointment with the trial information leaflet.Via telephone callThe clinical urological team or delegate may contact the patient and check whether he has received his NHS clinic appointment before sending out the information pack. After confirmation of receipt, the urological team or delegate (with appropriate Caldicott Guardian Approval) will introduce the study to the patient, and if they indicate interest, then an invitation pack will be sent.

If the patient declines the information pack or declines to provide a telephone number, no further attempt to recruit the patient will be made. The clinical or trial team will telephone patients who have agreed to be contacted. Any questions will be answered, and the patient will be asked whether he is interested in participating. The research team will arrange to see the patient for consent discussion. If required, the patient will be given additional time to consider participation before a final decision is made to arrange an appointment.

Patients will be advised to attend all of their planned scheduled appointments in the invitation letter and study introduction call. Prospective participants will be encouraged to telephone if they have any questions that they would like answered prior to attendance or to inform the research team if they change their minds with regard to participating. Patients who do not wish to participate will follow their local standard of care pathway.

#### Inclusion criteria

Males aged 40–75 years at referralHad an MRI scan within 3 months prior to recruitment: for sites with pre-biopsy MRI included in the standard of careWith at least 10 years’ life expectancy at clinical referralWith clinically localised PCa: PSA ≤ 20 ng/mlAnd/or with abnormal DRE but < T3 diseaseAbility to give informed consent

#### Exclusion criteria

Unable to give informed consentPrior prostatic biopsy within 12 monthsContraindications to biopsyPoor general health and life expectancy < 10 yearsPrevious diagnosis of acute prostatitis within 12 monthsHistory of PCaPrior transurethral prostatectomyContraindications to MRI, including cardiac pacemakers, allergic reaction to gadolinium-based contrast, renal failure, intracranial clips, claustrophobia (applicable to participants who do not receive MRI as part of the standard care pathway)Previous hip replacement

#### Ineligible and non-recruited participants

Ineligible patients or those who decide not to enter the study will receive the standard of care. The reason(s) for ineligibility will be explained to all individuals who express interest in the study. Any questions they have will be answered. A record of the number of patients screened will be kept that indicates the number of patients eligible/ineligible to participate.

#### Blinding

In this study, blinding of the biopsy performer on men randomised to MR/US fusion-guided biopsy is not feasible, but radiologists and pathologists will be double-blinded regarding the patients’ outcomes until the end of the statistical analyses.

### Allocations and interventions

All enrolled participants will be offered 1.5 Tesla or 3.0 Tesla mpMRI prior to prostate biopsy where this is not already within the standard care pathway. A subgroup of participants with positive pre-biopsy MRI will be randomised into two further subgroups at a 1:1 ratio. Randomisation will be via TRUST, a web-based, good clinical practice (GCP)-compliant randomisation system run by the Health Informatics Centre (HIC). Randomisation will be implemented with random block sizes stratified by site and minimised by: the Prostate Imaging Reporting and Data System (PI-RADS) suspicion score (3–5); index lesion size (in two categories: above and below 6 mm in maximal diameter on MRI); age (40–59 years, 60–75 years); and PSA < 10.1 or PSA ≥ 10.1 to ≤ 20 ng/ml). The first subgroup will undergo a TRUS and MRI/US fusion-guided biopsy and the second will undergo standard of care TRUS-guide biopsies only. The MRI/US fusion-guided biopsy will be performed during the same attendance as the TRUS-guided biopsy***.*** TRUS and MRI/US fusion-guided biopsies will be performed by NHS-accredited radiologists and/or urologists from the research team. The persons undertaking the biopsy will have prior experience and will have received appropriate training from clinical experts and/or the equipment supplier’s application specialist(s). Those participants with negative pre-biopsy MRI will follow the local standard of care pathway; where this includes biopsy, data from the biopsy will be collected for analysis.

In a subgroup of patients who undergo radical prostatectomy, the prostatectomy specimen will be sectioned using customised moulds [9, 10] allowing for direct comparison with mpMRI. This will be carried out in NHS Tayside, NHS Grampian and other sites where local facilities allow. Comparison of mpMRI with a reference standard of radical prostatectomy pathology will be performed as the primary outcome.

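### Two sections disagree on whether all of the roughly 120 MRI-negative men are biopsied, which leaves the secondary MRI accuracy comparison open to partial verification bias

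*Protocol article*

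**What the plan says.** Study population and setting divides participants by mpMRI result. It takes a suspicious lesion to be present in "80% of all pre-biopsy MRI scans", so about 480 of 600 men are randomised and "each of the two randomisation arms will have approximately 240 patients". The remaining group of about 120 "will undergo standard care (TRUS-guided biopsy) with histological comparative analysis".

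Allocations and interventions describes the MRI-negative men differently: they "will follow the local standard of care pathway; where this includes biopsy, data from the biopsy will be collected for analysis". Biopsy is conditional here. The condition has practical force, because Participant selection and enrolment opens with "As standard care pathways differ among sites".

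For MRI-positive men there is no such condition: "The first subgroup will undergo a TRUS and MRI/US fusion-guided biopsy and the second will undergo standard of care TRUS-guide biopsies only".

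The MRI-negative biopsies have a named use. Randomised controlled trial (Objective 2) lists, among its secondary outcomes, a comparison of them with the TRUS histology of MRI-positive men, in support of an analysis of MRI diagnostic accuracy.

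Identifying potential participants adds a recruitment route after standard-care mpMRI that is open only to men whose scan was positive.

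**The concern.** The two descriptions of the MRI-negative group cannot both hold. One has every such man biopsied; the other has some biopsied, depending on the site. The figure of about 120 fits only the first.

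Under the second, whether a man's disease status is verified by biopsy depends on the result of the test being evaluated. This is partial verification. Unbiopsied MRI-negative men drop out of the false-negative and true-negative cells, while the MRI-positive cells stay complete. If sensitivity and specificity are calculated from verified men without correction, sensitivity is inflated and specificity deflated, even if the choice of whom to biopsy has nothing to do with cancer. In a study that describes itself as one of diagnostic accuracy, a reader could take such figures at face value.

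**Working it through.** **The plan's own figures.** From Study population and setting: 1000 − 350 − 50 = 600 men scanned; 0.80 × 600 = 480 MRI-positive; 480 / 2 = 240 per arm; 600 − 480 = 120 MRI-negative. All reproduce. The 120 is therefore a count of negative scans. It is also the number biopsied only if every MRI-negative man is biopsied.

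**Inputs not in the document (assumptions).** The verified fraction f among MRI-negative men, and the cancer rates on biopsy: 40–60% in MRI-positive men (a) and 10–25% in MRI-negative men (b). All 480 MRI-positive men are taken as verified.

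**Formulas, verified men only, with f the same for men with and without cancer.**
- TP = 480a, FP = 480(1 − a), FN = 120fb, TN = 120f(1 − b)
- Sensitivity = TP/(TP + FN); specificity = TN/(TN + FP); negative predictive value (NPV) = TN/(TN + FN)

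Worked case, a = 0.40 and b = 0.25:
- f = 1: sensitivity 192/(192 + 30) = 0.865; specificity 90/(90 + 288) = 0.238
- f = 0.5: sensitivity 192/(192 + 15) = 0.928; specificity 45/(45 + 288) = 0.135

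Range over the four combinations of a and b:

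| f | Verified MRI-negative men | Sensitivity | Specificity |
|---|---|---|---|
| 1 | 120 | 0.865–0.960 | 0.238–0.360 |
| 0.75 | 90 | 0.895–0.970 | 0.190–0.297 |
| 0.5 | 60 | 0.928–0.980 | 0.135–0.220 |
| 0.25 | 30 | 0.962–0.990 | 0.072–0.123 |

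Within each combination, going from f = 1 to f = 0.5 raises sensitivity by 0.02–0.06 and lowers specificity by 0.10–0.14.

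**NPV and the MRI-negative detection rate.** With a common f, NPV = 120f(1 − b)/(120f) = 1 − b. It does not depend on f, so there is no bias, only lost precision. The 95% half-width is 1.96 × √(b(1 − b)/(120f)). Going from f = 1 to f = 0.5 widens it from ±5.4 to ±7.6 points at b = 10%, and from ±7.7 to ±11.0 points at b = 25%.

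Bias appears if biopsy is related to cancer. Suppose 70% of MRI-negative men with cancer and 40% of those without are biopsied:
- b = 10%: FN = 12 × 0.7 = 8.4; TN = 108 × 0.4 = 43.2; apparent NPV 43.2/51.6 = 0.84 against a true 0.90
- b = 25%: FN = 30 × 0.7 = 21; TN = 90 × 0.4 = 36; apparent NPV 36/57 = 0.63 against a true 0.75

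**Check that correction works.** In the worked case at f = 0.5, weighting each verified MRI-negative man by 1/f = 2 restores FN to 30 and TN to 90, and hence 0.865 and 0.238. This holds when verification is unrelated to cancer given the variables in the weights, and it requires f > 0.

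**The case against.** The strongest reply is that the article fixes no estimator for this secondary outcome. It says only that the two sets of biopsies are compared in support of an accuracy analysis. How unverified men are handled is commonly left to an analysis plan, which is not shown here. That stands: the absence of a correction method is not itself an error, and it would be wrong to say the article prescribes an uncorrected analysis of verified men. But no analysis plan removes the conflict between the two sections. Nor is the stratification by site and minimisation variables a verification correction, since it does not model who was biopsied.

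Three stronger readings are tempting and are not supported.

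- *The primary outcome is biased in the same way.* The article states: "Comparison of mpMRI with a reference standard of radical prostatectomy pathology will be performed as the primary outcome". That outcome has its own selection, among men who opt for surgery. It is a separate issue, and correcting biopsy-referenced accuracy would not address it.
- *Biopsied MRI-negative men are the higher-risk ones, so NPV is distorted.* The documents describe pathways that differ by site and say nothing of selection by risk. The bias in NPV and in the MRI-negative detection rate is conditional.
- *The bias can be sized from the 80% sensitivity in the sample-size statement, with a specificity of, say, 0.50.* That pair cannot produce the stated split: 0.8p + 0.5(1 − p) = 0.80 requires a prevalence p of 1.

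It is also fair to object that weighting fails at a site that never biopsies MRI-negative men, because the verification probability there is zero. The fix has to allow for this.

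**Conclusion.** The contradiction is certain. As the text stands, the number of biopsied MRI-negative men is undefined, and the group of about 120 may not be delivered; whether it falls short, and by how much, cannot be known from the article.

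If biopsy follows the local pathway and some MRI-negative men go unverified, uncorrected sensitivity and specificity for the secondary accuracy outcome are biased upwards and downwards respectively. At f = 0.5 specificity loses roughly 40% of its value (for example 0.135 against 0.238), while sensitivity moves little because it is already high. These sizes rest on assumed values of f and of the cancer rates, so they show scale and direction and are not estimates.

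The consequence is confined to one secondary outcome. The randomised comparison lies wholly within MRI-positive men and is untouched. The point should be corrected because the correction is cheap, but it does not threaten the trial's main results.

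**What to change.** 1. Reconcile Study population and setting with Allocations and interventions on which MRI-negative men are biopsied, and make the stated MRI-negative number agree with the reconciled text. Which pathway is right is a clinical matter on which this review takes no position.
2. Report the fraction of men verified by biopsy, by mpMRI result and by site.
3. If verification is incomplete, estimate biopsy-referenced sensitivity and specificity with the Begg-Greenes method or inverse-probability-of-verification weighting, using the mpMRI result and baseline variables (PSA, age, DRE). Limit this, for MRI-positive and MRI-negative men alike, to sites where some MRI-negative men are biopsied, since the weights are undefined elsewhere.
4. Exclude from this analysis, or handle separately, men recruited through the route open only to those with a positive scan. They have no MRI-negative counterparts, and weighting cannot supply men who were never enrolled.

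The cost is a wording change and modest programming. The downside is wider intervals and possibly a smaller stated MRI-negative number. The correction also assumes that, given the variables used, being biopsied is unrelated to cancer status, and this should be stated with the result.
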